# Neoadjuvant treatment of sintilimab plus hypofractionated radiotherapy for MSI‐H/dMMR rectal cancer: A prospective, multicenter, phase Ib study

**DOI:** 10.1002/cam4.4720

**Published:** 2022-03-29

**Keywords:** anti‐PD‐1 antibody, hypofractionated radiotherapy, neoadjuvant therapy, rectal cancer

## Abstract

**Background:**

Neoadjuvant radiochemotherapy followed by radical surgery is the standard treatment strategy for local advanced rectal cancer (LARC). However, the efficacy of neoadjuvant radiochemotherapy is limited, especially for patients with DNA mismatch repair‐deficient (dMMR)/microsatellite instability‐high (MSI‐H) rectal cancer. Considering the amazing therapeutic effect of immune check point inhibitors for metastatic colorectal cancer, we conduct this multicenter, phase Ib study to investigate the safety and efficacy of anti‐PD‐1 antibody, sintilimab combined with hypofractionated radiotherapy in MSI‐H/dMMR rectal cancer patients.

**Methods:**

Patients with MSI‐H/dMMR LARC will receive hypofractionated radiotherapy (5 Gy × 5) and three cycles of sintilimab 200 mg IV every 2 weeks. Radical surgery will be performed 6–8 weeks after radiotherapy. The primary endpoint is adverse reaction after neoadjuvant treatment and perioperative complications. Secondary endpoints include pathological response rate, complete resection rate, and quality of life.

**Discussion:**

This is the first study to investigate the safety and effectiveness of neoadjuvant radiotherapy combined with immunotherapy for MSI‐H/dMMR LARC. It is expected that this study will propose a brand new and effective treatment strategy for MSI‐H/dMMR LARC.

## INTRODUCTION

1

According to the latest statistics, colorectal cancer (CRC) is the fourth most common malignancy worldwide and the second leading cause of cancer‐related deaths.^1^ Local advanced rectal cancer (LARC), defined as stage II or III rectal cancer, accounts for a considerable proportion in CRC. Due to the special anatomic location and difficulties in obtaining wide resection margins, LARC has relatively high risk of locoregional recurrence. Therefore, local radiotherapy, which is associated with a decreased local recurrence rate, is recognized as an important treatment approach for LARC. Actually, preoperative concurrent chemoradiotherapy with fluorouracil, total mesorectal excision (TME) surgery, followed by adjuvant chemotherapy has become the standard treatment for LARC.^2^

Several large phase 3 trials have demonstrated the benefit of preoperative fluoropyrimidine‐based chemotherapy with radiation, such as down staging, increasing complete resection rate, and improving pathological/clinical complete response (pCR/cCR) rate.^3^, ^4^, ^5^, ^6^, ^7^ It is generally acknowledged that pCR/cCR is associated with long‐term survival benefit and organ preservation. Hence, pCR/cCR rate is a vital factor for evaluating the effectiveness of preoperative neoadjuvant treatment in LARC. However, previous large random trials have indicated that pCR rate of neoadjuvant concurrent chemoradiotherapy with fluorouracil is very limited, ranging from 8% to 17%. In recent years, to improve the efficacy of neoadjuvant treatment, investigators have tried to intensify chemotherapy regimen, such as adding oxaliplatin, irinotecan, or total neoadjuvant therapy (TNT), in suitable patients with good physical status. Although pCR rate has improved to 19%–30%, the long‐term benefits of disease‐free survival (DFS) and overall survival (OS) have not changed.^8^, ^9^, ^10^, ^11^, ^12^, ^13^ Besides, chemotherapy intensification has increased adverse events remarkably. Thus, it is of great significance to explore a new preoperative treatment pattern to increase the possibility of anal sphincter preservation, improve long‐term survival and the quality of life.

For the past few years, immune checkpoint inhibitors, including anti‐PD‐1, anti‐PD‐L1, and anti‐CTLA4 antibodies, have shown amazing effect in multiple kinds of malignant tumors. Growing evidence supports that metastatic CRC patients with deficient mismatch repair proteins (dMMR) or high microsatellite instability (MSI‐H) are sensitive to immunotherapy.^14^, ^15^, ^16^, ^17^, ^18^ In the trial of CheckMate 142, nivolumab, an anti‐PD‐1 immune checkpoint inhibitor, shows durable response in previously treated dMMR/MSI‐H CRC patients, with the objective response rate (ORR) of 31.1%, disease control rate (DCR) of 69%, and median progression‐free survival (PFS) of 14.3 months.^15^ Given the excellent effect of immunotherapy, National Comprehensive Cancer Network (NCCN) guideline has recommended nivolumab or pembrolizumab as second‐line or more treatment for metastatic MSI‐H/dMMR CRC patients in the year of 2017. Last year, the randomized, phase 3 trial Keynote 177 have demonstrated the safety and efficacy of pembrolizumab as first‐line treatment for metastatic dMMR/MSI‐H CRC patients.^18^ Compared to chemotherapy, pembrolizumab has shown significantly longer PFS (16.5 vs. 8.2 months; hazard ratio [HR], 0.60; *p* = 0.0002).^18^ At present, immunotherapy is recommended as standard treatment for metastatic dMMR/MSI‐H CRC patients. In recent years, researchers have endeavored investigating immunotherapeutic effect in early‐stage of CRC patients with dMMR/MSI‐H. Preliminary results for NICHE trial reveals amazing neoadjuvant treatment efficacy of PD‐1 plus CTLA‐4 inhibition in early‐stage of dMMR/MSI‐H colon cancer (pCR rate: 57.1%).^19^ However, the role of immunotherapy in the neoadjuvant setting for rectal cancer is still unknown.

Additionally, increasing evidence suggests that radiotherapy, especially hypofractionated radiotherapy, has synergistic effect with immunotherapy.^20^, ^21^, ^22^, ^23^ The results of KEYNOTE‐001 trial indicate that patients treated with pembrolizumab who previously received radiotherapy have longer OS and PFS than patients who did not receive any radiotherapy (median PFS, 4.4 vs. 2.1 months; HR, 0·56, 95% CI: 0·34–0·91, *p* = 0·019; median OS, 10·7 vs. 5.3 months; HR, 0·58, 95% CI: 0·36–0·94; *p* = 0·026).^23^ The study performed by Kiess AP et al. demonstrates better survival in brain metastatic melanoma patients receiving stereotactic radiotherapy combined with ipilimumab immunotherapy, when compared to previous studies of melanoma patients treated with radiotherapy alone or ipilimumab alone.^22^

Considering good response of immunotherapy in metastatic MSI‐H/dMMR CRC patients and synergistic effect of immunotherapy combined with radiotherapy, we conduct this study to prospectively investigate the safety and efficacy of anti‐PD‐1 antibody (sintilimab) combined with hypofractionated short‐course radiotherapy as neoadjuvant treatment for dMMR/MSI‐H LARC.

## STUDY DESIGN AND METHODS

2

### Study design and treatment

2.1

This study is a prospective, multicenter, single‐arm, phase Ib trial to explore the safety and effectiveness of neoadjuvant treatment with sintilimab plus hypofractionated radiotherapy for dMMR/MSI‐H LARC patients. The study has obtained ethics approval and is currently ongoing in five large‐capacity hospitals in China. The main inclusion criteria are histologically confirmed local advanced rectal adenocarcinoma (no distant metastasis and clinical T stage ≥T2 on radiographic imaging), dMMR or MSI‐H status, without any anticancer treatment previously, ECOG performance status 0 or 1, age ≥18 years, and adequate organ function. Informed consent will be obtained from every subject who volunteers to participate. The main exclusion criteria include allergic or autoimmune disease history, other malignant tumor history with DFS <5 years, immunosuppressant or corticosteroid use within 2 weeks before inclusion. Complete inclusion and exclusion criteria are shown in Table 1.

**TABLE 1 cam44720-tbl-0001:** Patient inclusion and exclusion criteria

Inclusion criteria	Exclusion criteria
1. Histologically confirmed rectal adenocarcinoma 2. With DNA mismatch repair‐deficient (dMMR) or microsatellite instability‐high (MSI‐H) status, whether or not being Lynch syndrome 3. Not received any anti‐rectal cancer treatment previously; for patients with Lynch syndrome, not received any antitumor therapy about rectal cancer diagnosed this time 4. No distant metastasis except for lateral lymph nodes on thoracic and abdominal enhanced computed tomography (CT) scans; the distance between tumor's lower edge and anus within 15 cm; clinical T stage ≥T2 on high‐resolution pelvic magnetic resonance imaging (MRI) 5. Men and women ≥18 years of age 6. Eastern Cooperative Oncology Group performance status score 0 or 1 7. Adequate hematologic, hepatic, renal, thyroid, and cardiac function: hemoglobin ≥90 g/L, neutrophils ≥1500/mm^3^, platelets ≥75,000/mm^3^; aspartate aminotransferase and alanine aminotransferase ≤3.0 × upper limit of normal (ULN), bilirubin ≤1.5 × ULN; creatinine ≤1.5 × ULN, creatinine clearance ≥50 ml/min; activated partial thromboplastin time, prothrombin time and international normalized ratio ≤1.5 × ULN; serum albumin ≥28 g/L; thyroid stimulating hormone and free thyroxine within ±10% of normal levels; no obvious abnormality in electrocardiogram 8. Not received blood, blood products, and hematopoietic growth factor (e.g., granulocyte colony‐stimulating factor) within 2 weeks before inclusion 9. Informed consent form signed 10. Life expectancy of ≥3 months	1. Allergic disease history, severe hypersensitivity to drugs, antibody products or sintilimab 2. Other malignancy history with disease‐free survival <5 years, except for curative in situ cervical cancer, curative skin basal cell carcinoma and curative gastrointestinal cancer by endoscopic mucosal resection 3. Current or past history of autoimmune diseases, including but not limited to: interstitial lung disease, uveitis, enteritis, active hepatitis (HBV DNA ≥10^3^ copies/ml after regular antiviral therapy), nephritis, hyperthyroidism, and hypothyroidism 4. Immunosuppressant or corticosteroid (systemic or local) use to suppress immune function within 2 weeks before inclusion 5. Severe infection needing intravenous antibiotics, antifungal agents, or antiviral drugs, et al 6. Congenital or acquired immunodeficiency such as HIV infection; active Hepatitis B (HBV DNA ≥10^3^ copies/ml after regular antiviral therapy) 7. Having one of the following complications: massive gastrointestinal hemorrhage, gastrointestinal perforation, or obstruction; symptomatic heart diseases including unstable angina, myocardial infarction, and heart failure; uncontrollable diabetes mellitus or hypertension; uncontrollable diarrhea (interfering with daily activities although receiving adequate treatment) 8. Bleeding tendency or receiving thrombolytic or anticoagulant therapy 9. Pregnant or breastfeeding female; male and female unwilling to take any contraceptive measures 10. Psychiatric disorders that would interfere with cooperation with the requirements of the study 11. Other conditions that investigators consider not suitable for this study

Patients eligible for participation in the trial will receive three cycles of sintilimab combined with concurrent radiotherapy. Sintilimab is administered at a dose of 200 mg intravenously every 2 weeks. Hypofractionated short‐course radiotherapy consists of 25 Gy in five fractions using intensity‐modulated radiotherapy (IMRT). Delayed radical surgery will be performed 6–8 weeks after radiotherapy. Patients who obtain cCR after careful evaluation could choose watch & wait strategy in order to preserve anal sphincter. The study design is depicted in Figure 1. Fluorouracil‐based adjuvant chemotherapy will be administered after surgery according to the NCCN guidelines.

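### The article defines LARC as stage II or III, but its entry rule (cT≥T2, M0, no nodal or stage condition) also admits stage I (cT2N0), so full-cohort results are not restricted to LARC as defined

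*Protocol article*

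**What the plan says.** The Introduction gives the definition: "Local advanced rectal cancer (LARC), defined as stage II or III rectal cancer". The abstract, the aims and section 2.1 all name MSI-H/dMMR LARC as the population. The Discussion sets the trial apart from others on the ground that it takes only such patients.

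Section 2.1 lists the main inclusion criteria. It asks for locally advanced adenocarcinoma and, in parentheses directly after that term, gives "no distant metastasis and clinical T stage ≥T2 on radiographic imaging". It then refers the reader onward: "Complete inclusion and exclusion criteria are shown in Table 1".

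In Table 1, criterion 1 reads "Histologically confirmed rectal adenocarcinoma", without the words locally advanced. Criterion 4 asks for cT≥T2 on pelvic MRI, a lower tumour edge within 15 cm of the anus, and "No distant metastasis except for lateral lymph nodes on thoracic and abdominal enhanced computed tomography (CT) scans". Lateral nodes appear there as a permitted exception. Node-positive disease is nowhere required, and none of the eleven exclusion criteria removes a cT2N0 tumour.

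Section 2.2 makes safety (adverse events during neoadjuvant therapy and perioperative complications) the primary endpoint, with cCR/pCR rate among the secondary endpoints. Section 2.3 plans 20 subjects without a formal sample size calculation.

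**The concern.** The label and the rule describe different sets of patients. A single-arm trial has no internal comparator, so its results are read through the description of who was treated. The abstract expects the study to propose a treatment strategy for MSI-H/dMMR LARC. If some of the 20 patients are stage I, the full-cohort adverse event rate, complication rate and cCR/pCR rate would be presented as LARC results although part of the denominator is not LARC by the article's own definition.

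The primary endpoint could be touched as well as the response rate. Patients with cCR may choose watch & wait, so if response depends on stage, stage mix also affects who reaches surgery and can have a perioperative complication.

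**Working it through.** **Step 1. Rule against definition.** The article states no derived figure on this point, so the check is to set the two texts side by side. The stage grouping in the second column is standard TNM; the article does not spell it out. All rows are M0.

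| Clinical category | TNM stage | LARC by the Introduction | Meets the T and M rule in Table 1 |
|---|---|---|---|
| cT1N0 | I | no | no |
| cT1N+ | III | yes | no |
| cT2N0 | I | **no** | **yes** |
| cT2N+ | III | yes | yes |
| cT3-4N0 | II | yes | yes |
| cT3-4N+ | III | yes | yes |

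Of the four admitted categories, three are stage II-III and one, cT2N0, is not.

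**Step 2. What stage I patients could do to the results.** The article gives neither the number k of cT2N0 patients among the 20 nor any outcome by stage. The values of k, the event rate and the response rates below are assumptions, used only to show scale.

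*Safety information on LARC.* With n = 20 − k LARC patients, the chance of seeing at least one event of true rate 10% is 1 − 0.9^n. The one-sided 95% upper bound after zero events is 1 − 0.05^(1/n).

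| k | n | Chance of at least one event | Upper bound if none |
|---|---|---|---|
| 0 | 20 | 87.8% | 13.9% |
| 2 | 18 | 85.0% | 15.3% |
| 4 | 16 | 81.5% | 17.1% |
| 6 | 14 | 77.1% | 19.3% |
| 10 | 10 | 65.1% | 25.9% |

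*Pooled complete response.* The pooled rate is [(20 − k)·r + k·q]/20, where r is the rate in stage II-III and q the rate in cT2N0. The shift away from r is therefore (k/20)·(q − r). Take r = 60%, which matches the 3/5 dMMR patients cited in the Discussion from another trial, and q from 60% to 90%:

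- k = 0: 60% whatever q is, so no shift.
- k = 4: 0.8 × 60% + 0.2 × q = 60% to 66%, a shift of 0 to 6 points.
- k = 10: 0.5 × 60% + 0.5 × q = 60% to 75%, a shift of 0 to 15 points.

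The shift is zero when k = 0 or q = r, and its sign is that of q − r. The article supplies neither k nor q.

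**The case against.** The strongest reply is that section 2.1 does ask for locally advanced disease, so its parenthesis might be read as adding conditions to LARC rather than defining it. That reading does not hold up: Table 1 is called complete, and it drops the term without putting a stage or nodal condition in its place.

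It can also be said that the article has no test or decision rule on cCR/pCR. The rates of 8-17% and 19-30% in the Introduction come from chemoradiotherapy or intensified chemotherapy, so they differ in regimen as well. With 20 patients, the exact 95% interval around 50% runs from about 27% to 73%. All this stands, and it limits the weight of the point. It does not repair the label, because a wide interval still has to refer to a stated population.

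A reader might infer more than the documents support:

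- *That the results do not apply to LARC.* Three of the four admitted categories are stage II-III, and the cohort may contain no cT2N0 patient at all.
- *That the response rate will be inflated by a known amount.* The article does not say that cT2N0 tumours respond better to this regimen, and gives no stage mix.
- *That the lateral-node wording makes a second contradiction.* Section 2.1 lists only main criteria and defers to Table 1, which states the exception openly.
- *That shutting out cT1N+ is part of the error.* A trial may take a subset of its disease category, and patients who are not enrolled cannot make the cohort non-LARC.

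**Conclusion.** The point holds as an inconsistency between the Introduction's definition and the Discussion's claim on one side, and section 2.1 and Table 1 on the other. Stage I (cT2N0M0) patients qualify, so the full-cohort safety and cCR/pCR results are not restricted to LARC as the article defines it. This rests on the published text and on the standard TNM grouping, not on any assumed rate.

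The size is unknown and may be zero. No number stated in the article changes. What changes is which population a conclusion may name. Which entry rule is clinically right is not judged here.

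**What to change.** Reconcile the LARC definition with the entry criteria, so that the Introduction, section 2.1, Table 1 and the Discussion describe one population.

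If the cT≥T2 rule stands:

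- describe the full cohort as cT≥T2 M0 rectal cancer, with the lateral-node exception as in Table 1;
- report safety and cCR/pCR by baseline clinical stage;
- draw statements about LARC only from the stage II-III patients, with cT2N0 shown separately.

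This route alters no patient's entry or care and can be taken although the trial is already running in five hospitals. It costs a wording correction, one extra table and a smaller denominator for the LARC statements. In the illustration above, with 4 of 20 patients stage I, the zero-event upper bound for LARC would be 17.1% instead of 13.9%.

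If the sponsor instead changes the criteria to match the definition, that is an amendment to an ongoing trial whose size was set by scarce accrual. Any cT2N0 patients already enrolled would still need to be shown separately.

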**FIGURE 1 cam44720-fig-0001:**
[figure not shown]
Outline of the study design

### Endpoints and assessments

2.2

The primary endpoint is treatment safety in terms of adverse event rate during neoadjuvant therapy and perioperative complication probability. Secondary endpoints include treatment efficacy measured with cCR/pCR rate, complete resection rate, and quality of life.

Subjects will be visited every 2 weeks to collect data about symptoms, treatment regimen, drug combination, physical and laboratory examinations, quality of life, and adverse events. Adverse events will be evaluated throughout the trial and at 28 days after treatment discontinuation or drop out, which will be graded according to the Common Terminology Criteria for Adverse Events (CTCAE) version 5.0. The quality of life will be evaluated before every cycle of sintilimab infusion, before and after 1 month of surgery, using validated questionnaires, that is European Organization for Research and Treatment of Cancer Quality of Life Core Questionnaire 30 and European Organization for Research and Treatment of Cancer Quality of Life Questionnaire‐Colorectal Cancer 29. Imaging evaluation by CT and magnetic resonance imaging (MRI) will be performed at baseline and 6–8 weeks after end of radiotherapy.

For subjects obtaining cCR after neoadjuvant treatment, organ preservation strategy should be adopted prudently after careful assessment with digital examination, endoscopy, chest CT, abdominal CT, and pelvic MRI. A multidisciplinary team evaluation is recommended. The cCR is defined as the absence of any palpable tumor at digital rectal examination; no visible lesion at endoscopy except a flat scar, telangiectasia or mucosa whitening and negative biopsies from the scar; and residual tumor absence on imaging with MRI or endoscopic rectal ultrasound (ERUS).^24^

The expression of four mismatch repair proteins (MLH1, MSH2, MSH6, and PMS2) is determined locally by immunohistochemical analysis. And if one or more of the four proteins is absent, the tumor status is defined as dMMR. MSI status is determined locally by polymerase chain reaction (PCR) analysis of five tumor microsatellite loci (NR‐21, NR‐24, BAT‐25, BAT‐26, and MONO‐27). And if two or more of the five loci are present, the tumor status is classified as MSI‐H.

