### Sample size and statistical analyses

2.3

As the primary end point of this phase Ib study is treatment safety, no formal sample size calculation is performed. Based on the low incidence of dMMR/MSI‐H LARC and expected number of patients in our research institutes, we plan to enroll 20 subjects in total. SPSS Statistics version 22.0 (IBM) will be used to perform all the statistical analyses.

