At present, there are several trials investigating the value of neoadjuvant immunotherapy in rectal cancer. For LARC patients with microsatellite stable (MSS), the study performed by Shamseddine A. et al. reveals promising efficacy of short‐course radiotherapy followed by mFOLFOX6 chemotherapy plus avelumab (anti‐PD‐L1 antibody), with a pCR rate of 25% (3/12).^29^ In the single‐arm, phase II study conducted by Lin Z. et al., LARC patients receiving short‐course radiotherapy with capecitabine and oxaliplatin chemotherapy plus camrelizumab (anti‐PD‐1 antibody) have a relatively high pCR rate of 48.1% (13/27), including 46.2% (12/26) for patients with proficient mismatch repair (pMMR) status and 100% (1/1) for dMMR patient.^30^ Preliminary results of VOLTAGE trial where 41 LARC patients receive long‐course radiotherapy with concurrent capecitabine chemotherapy followed by five cycles of nivolumab (anti‐PD‐1 antibody), shows a pCR rate of 30% in pMMR patients (11/37) and 60% in dMMR patients (3/5) with mild toxicities.^31^ Although these results show favorable safety and efficacy of preoperative immunotherapy, most patients in the trials are MSS/pMMR, with only a few MSI‐H/dMMR patients. Besides, their treatment approaches contain chemotherapy as well. The phase 2 trial conducted by Hu H. et al. reveals favorable pCR rate of neoadjuvant toripalimab with or without celecoxib in MSI‐H locally advanced colorectal cancer patients. But this trial mainly enrolls colon cancer patients (30/36), with only six rectal tumors.^32^ In contrast, our study will only enroll MSI‐H/dMMR LARC patients and get rid of chemotherapeutic agents. We believe this study will illustrate the safety and effectiveness of radiotherapy combined with immunotherapy in MSI‐H/dMMR LARC patients, and propose a brand new treatment approach for this specific group of patients.

There are several limitations in our study, including a small sample size, lack of a control group, and uncertain pathological examination after neoadjuvant treatment in patients who choose watch & wait strategy.

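### The MSI-H rule counts loci that are present rather than unstable, so the article's only working definition of MSI-H does not, as worded, exclude a stable tumour

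*Protocol article*

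**What the plan says.** Section 2.2 (Endpoints and assessments) gives one rule for each biomarker.

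- **Mismatch repair, by immunohistochemistry:** "if one or more of the four proteins is absent, the tumor status is defined as dMMR".
- **Microsatellites, by PCR:** "MSI status is determined locally by polymerase chain reaction", through "analysis of five tumor microsatellite loci", which the article names. The decision rule is that "if two or more of the five loci are present, the tumor status is classified as" MSI-H.

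Table 1, inclusion criterion 2, requires dMMR "or microsatellite instability‐high (MSI‐H) status, whether or not being Lynch syndrome". The two markers are joined by *or*, so either one is enough. The Abstract expands MSI-H in the same way as Table 1, with the word instability in the name.

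The Discussion treats microsatellite-stable patients as a separate population studied in other trials and says "our study will only enroll MSI"-H/dMMR disease. No other part of the article says how a PCR result becomes an MSI-H classification.

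**The concern.** The mismatch repair rule names an abnormality, the absence of a protein. The MSI rule names none. It asks whether loci are present, and presence says nothing about stability. The property that gives MSI-H its name does not appear in the rule that assigns it.

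The sentence bears on who can enter the trial. The article's rationale is that dMMR/MSI-H tumours respond relatively poorly to fluoropyrimidine chemotherapy and well to immunotherapy. A stable tumour admitted under the literal wording would be treated outside that rationale, in a neoadjuvant phase that contains no chemotherapy. The patient would also be counted in the safety and response results reported for MSI-H/dMMR disease. Results are read locally, and section 2.1 places the trial in five hospitals, so several laboratories may work from this definition.

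**Working it through.** The plan has no figure to reproduce here. Section 2.3 states that "no formal sample size calculation is performed", and the planned 20 subjects is a feasibility number that does not depend on this rule. The check is to apply the rule as worded, follow the result to eligibility, and compare it with the rest of the article.

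**Inputs**

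- Panel: 5 loci (section 2.2).
- Threshold: at least 2 of 5 (section 2.2).
- Eligibility: dMMR or MSI-H (Table 1, inclusion criterion 2).
- Assumption: *present* has its ordinary meaning, that the site is there and detected by the PCR.

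**Step 1. Apply the rule.** Take tumours in which all five loci are evaluable.

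| Unstable loci | Loci present | Rule as worded (present ≥ 2) | Rule counting unstable loci (≥ 2) |
|---|---|---|---|
| 0 | 5 | 5 ≥ 2: MSI-H | 0 < 2: not MSI-H |
| 1 | 5 | 5 ≥ 2: MSI-H | 1 < 2: not MSI-H |
| 2 | 5 | 5 ≥ 2: MSI-H | 2 ≥ 2: MSI-H |
| 5 | 5 | 5 ≥ 2: MSI-H | 5 ≥ 2: MSI-H |

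The third column is the same in every row. As worded, the rule fails only when fewer than two loci are detected, so it depends on whether the assay worked and not on the state of the tumour.

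**Step 2. Follow it to eligibility.** Take the first row with all four mismatch repair proteins retained. The dMMR limb is not met and the MSI-H limb is met as worded. Since the criterion is an *or*, inclusion criterion 2 is satisfied. The remaining criteria in Table 1 still apply, but none of them concerns mismatch repair or microsatellite status.

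**Step 3. Compare with the rest of the article.**

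- The Abstract and Table 1 define the term by instability; the rule in section 2.2 does not mention it.
- Section 2.3 explains the small sample by how rare dMMR/MSI-H rectal cancer is. Under the literal rule almost every tumour with an evaluable assay would be MSI-H, which cannot be squared with rarity.
- The Discussion restricts enrolment to MSI-H/dMMR disease, while the literal rule would let in stable disease.

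All three comparisons show that instability was meant and that the sentence does not say so.

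**The case against.** The strongest reply is that this is a slip that no laboratory would follow. The name of the marker, the statement that PCR determines MSI status, the contrast with stable disease in the Discussion and the rarity argument in section 2.3 all point to one meaning. A laboratory running this panel would probably score instability whatever the article says. This stands, and it lowers the chance of harm. It does not make the sentence right. Nor is this detail that a condensed article leaves to the full protocol: the article chose to give panel, threshold and rule, and gave the rule wrongly.

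A reader might infer more than the documents support:

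- **That stable tumours have been or will be enrolled.** Nothing shows this. The error is shown in a sentence, not in any laboratory reading.
- **That the response rate will be diluted by a calculable amount.** With "we plan to enroll 20 subjects in total", one patient is 1/20 = 5% of the sample, but the documents give no count of misclassified patients. The response rates by mismatch repair status in the Discussion come from other regimens and small groups, such as 3/5 dMMR patients in one trial. Response is also a secondary endpoint with no threshold stated in the article; the primary endpoint is safety.
- **That such a patient would receive no chemotherapy at all.** Section 2.1 plans fluorouracil-based adjuvant chemotherapy after surgery. Only the neoadjuvant phase is free of it.
- **That local reading is itself a fault.** The article mentions no central confirmation, but a condensed article need not, and local testing would be unobjectionable under a correctly worded rule.

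**Conclusion.** The point holds as an error of wording in an eligibility definition. Read literally, the MSI-H rule does not separate unstable from stable tumours, contradicts the article's own name for the marker, and would let a stable tumour meet the biomarker part of inclusion criterion 2 on a local PCR result alone.

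The conclusion rests on the ordinary meaning of *present* and on this being the only operational definition of MSI-H in the article. The full protocol and any laboratory manual are not shown and may already be correct. It is probably a slip, with no evidence that anyone was wrongly enrolled. No sample size or endpoint changes, and the documents do not allow an effect on the results to be put into numbers. It should still be corrected, because the rule decides who belongs to the population the trial claims to study.

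**What to change.** In section 2.2, replace the presence condition with instability. For example: *If two or more of the five loci show instability, the tumour is classified as MSI-H; a tumour with 0 or 1 unstable loci is not MSI-H.* Make the same correction in the full protocol or laboratory instructions if they carry the same sentence.

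For any patient admitted on PCR alone, confirm from the report on file that at least two loci were unstable. This is a precaution, since nothing suggests that the rule was misapplied.

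The correction should not add a comparison with normal tissue. The article mentions only tumour loci, and such a requirement could mean extra testing that this point does not call for.

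The cost is one sentence and a review of existing reports. No new tests are needed, and the sample size and endpoints stay as they are.
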